### Process evaluation

Each part of the intervention delivered by the community health workers will be monitored and registered. This qualitative data will be gathered from registration forms. In the end, focus groups will be carried out with the elderly and their informal care givers, the community health workers, and the stakeholders in the (semi) urban residential areas.

### Data analysis

The data will be analysed using SPSS version 20. We compare the use of health care and social welfare facilities, quality of life, and functional impairments between the intervention group and the control group. To correct for the clustering of participants within wards and for baseline characteristics, multilevel analysis will be used to evaluate differences in outcome between the two groups regarding baseline and follow up measurements. Estimates will be performed with 95% confidence intervals. An intention-to-treat analysis will be conducted consisting of data from all subjects including those lost to follow up. Audio recordings of the focus groups will be transcribed verbatim and analysed thematically using NVivo version 9.

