**Methods/design:**

In a quasi experimental design, the effectiveness of introduction of community health workers, health needs assessment, and follow-up intervention programme will be evaluated in three (semi) urban residential areas in the Netherlands and compared with a control group. Community health workers are selected from local ethnic communities and trained for the intervention. Data on health perception, quality of life, and care consumption are collected at baseline and after the intervention programme. Elderly’s informal care givers are included to examine caregiver burden. The primary outcome is use of health care and social welfare facilities by the elderly. Secondary outcomes are quality of life and functional impairments. The target number of participants is 194 immigrant elderly: 97 for the intervention group and 97 for the control group. Implementation of the intervention programme will be examined with focus groups and data registration of community health worker activities.

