## Methods

### Design and setting

We conduct a quasi experiment with a pre-post test design with an intervention group and control group in three (semi) urban residential areas in the Netherlands with each a concentration of immigrants. The intervention consists of selection and training of community health workers, assessment of health needs, and follow-up intervention programme coordinated by the community health workers.

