### Control group

In order to assess the effectiveness of the intervention, the effects of introduction of the community health worker will be compared with a group where the community health worker is not introduced. No community health worker involvement is provided to the controls. The control group consists of a matched group comparable in size and composition. All controls live outside the three (semi) urban residential areas in the Netherlands that take part in the intervention. We use data from the ongoing Symbol study (Systematic Memory testing Beholding Other Languages) in the Netherlands to collect data on Turkish and Moroccan controls. Recruitment of Moluccan controls will be completed through bilingual interviewers in collaboration with a local social welfare organisation that serves Moluccan elderly.

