## Discussion

In the development of this study we made a number of choices that need to be addressed. We chose a quasi experiment, because a randomised controlled trial is less suitable for community-based intervention research using community health workers [42]. A randomised controlled trial whereby the community health workers randomise participants to specific conditions is difficult to translate into practice, because this may conflict with their role as a community health advocate due to the assignment to control conditions with no direct benefit to the community members they serve [42].

For the generalisability of our findings, we chose for diversity in immigrant populations (migrant background) and sites (semi large urban residential areas) and we recruited several community health workers on each site to deliver the intervention.

To ensure a representative reflection of elderly immigrants in the Netherlands, the three immigrant populations in this study were chosen, because these together represent the majority of the elderly immigrant population in the Netherlands. The three (semi) urban residential areas in the Netherlands were selected, because of the concentration of the immigrant populations involved in this study. The diversity in immigrant populations and the enrolment of multiple community health workers provide the opportunity to compare the results between three different locations with each a specific concentration of migrants and to examine if and under which conditions the community health worker have impact on the outcome measures.

The outcomes measures in this study were chosen to ensure that the effectiveness of the intervention is assessed on outcomes that are directly relevant for elderly immigrants. The health problems among elderly immigrants often lead to long-lasting functional limitations and need for health care [23]. Functional limitations and perceived health may have impact on their daily functioning and quality of life [3].

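### The programme is allocated by residential area, but the model corrects for clustering in undefined wards; the plan should model the allocation unit with small-sample inference

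*Protocol article*

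**What the plan says.** All references are to the protocol article.

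- **Delivery.** The abstract says the programme "will be evaluated in three (semi) urban residential areas in the Netherlands and compared with a control group". Under Intervention programme, steps 3 and 4 have local providers develop new initiatives and build them into their own services. The programme therefore changes what an area offers, as well as supporting individuals.
- **Controls.** The Control group section states: "All controls live outside the three (semi) urban residential areas in the Netherlands that take part in the intervention". Turkish and Moroccan controls come from another project ("We use data from the ongoing Symbol study"). Moluccan controls come by a separate route ("Recruitment of Moluccan controls will be completed through bilingual interviewers in collaboration with a local social welfare organisation").
- **Design.** Design and setting, read alone, could place both groups in the same areas: "with an intervention group and control group in three (semi) urban residential areas in the Netherlands".
- **Model.** Data analysis says "To correct for the clustering of participants within wards and for baseline characteristics, multilevel analysis will be used", with 95% confidence intervals. This is the only use of the word wards.
- **Sample size.** An effect size of 0.40, alpha 0.05 and beta 0.20 give 97 per group. No allowance for clustering is mentioned.
- **Locations.** The Discussion expects the design to make it possible to "compare the results between three different locations with each a specific concentration of migrants".

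**The concern.** Because no area contains both groups, area is nested in arm. The comparison of arms is a comparison of areas, and its precision depends on how much outcomes vary between areas and how many areas there are. A random effect removes the correlation at the level it represents, and no higher. The stated level is one the article neither defines nor connects to the three areas, to the areas where controls live, or to the two control sources.

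Two things are at stake. The confidence interval for the primary comparison may be narrower than the data justify. And a change in local services or policy during the 18 months of follow-up in one or more areas could be reported as a programme effect.

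**Working it through.** **Inputs from the article:** three intervention areas; all controls elsewhere; 97 per arm; effect 0.40 SD; alpha 0.05; power 0.80.

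**Assumptions (the article gives none of these):** three control areas; two or four wards per area; equal cluster sizes; area ICC 0 to 0.05; ward ICC 0.01. The ICCs refer to the quantity analysed (change, or baseline-adjusted follow-up), with SD 1.

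**1. The plan's own figure.** n = 2 × ((1.96 + 0.842)/0.40)² = 98.1, so 99 per arm. The stated 97 lies within two of this and has 79.6% power. It is the two-sided calculation for independent individuals, with a design effect of 1.

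**2. Wards as parts of areas, only ward modelled.** Let a and w be the area and ward ICCs, k the wards per area, K = 3k the wards per arm and m = 97/K the people per ward.

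- True variance of an arm mean: a/3 + w/K + (1 − a − w)/97
- Variance estimated from ward means: [w + (1 − a − w)/m + a(K − k)/(K − 1)]/K

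Example with k = 4, a = 0.05, w = 0.01:
- true: 0.01667 + 0.00083 + 0.00969 = 0.02719
- estimated: (0.01 + 0.1163 + 0.0364)/12 = 0.01355
- the true standard error is √(0.02719/0.01355) = 1.42 times the estimated one.

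Example with k = 2, a = w = 0.01:
- true: 0.00333 + 0.00167 + 0.01010 = 0.01510
- estimated: (0.01 + 0.0606 + 0.008)/6 = 0.01310
- ratio √(0.01510/0.01310) = 1.07.

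Rejection rates with no true effect, simulated from ward means (100,000 trials per setting, t reference on 2K − 2 degrees of freedom, w = 0.01):

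| Area ICC | 2 wards per area | 4 wards per area |
|---|---|---|
| 0 | 5.0% | 5.1% |
| 0.01 | 6.4% | 7.6% |
| 0.02 | 7.9% | 9.9% |
| 0.05 | 10.9% | 15.9% |

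A t-test on area means (4 degrees of freedom) stays at about 5% in every row. Assuming six control areas instead of three helps little: with four wards per area, the ward-level test rejects 6.9%, 8.9% and 14.5% at area ICC 0.01, 0.02 and 0.05.

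**3. Wards as another word for the areas.** The level is then right. With three clusters per arm, a random-intercept model with a large-sample normal reference rejects about 5.8%, 7.3% and 9.9% at area ICC 0.01, 0.02 and 0.05. The t-test on area means holds 5%.

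**4. Power when the allocation unit is modelled.** The design effect is DE = 1 + (97/3 − 1) × ICC, the standard error is √(2 × DE/97), and the test is t with 4 degrees of freedom (critical value 2.776).

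| Area ICC | DE | SE | 0.40/SE | Power |
|---|---|---|---|---|
| 0.01 | 1.31 | 0.165 | 2.43 | 46% |
| 0.02 | 1.63 | 0.183 | 2.18 | 39% |
| 0.05 | 2.57 | 0.230 | 1.74 | 27% |

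These treat 0.40 as the plan's calculation does, without any gain from baseline adjustment, which would raise them.

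**The case against.** The strongest defence is that wards may simply mean the residential areas. Those are the only geographic units the article describes, and no smaller unit is mentioned. On that reading the model already sits at the allocation level. The degrees-of-freedom method is also the kind of detail an article leaves to the full protocol or SAP, so silence on it is not an error. This stands in part: a reader might infer that the planned standard errors are too small as a matter of fact, and the article does not support that. It depends on wards being smaller than areas and on area variance above zero. What remains is that the article does fix a cluster level, in a term that cannot be matched to its own allocation unit or to the controls.

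Second, confounding of area with intervention follows from an openly declared design ("We conduct a quasi experiment with a pre-post test design with an intervention group and control group"), with matched controls and baseline adjustment. That is fair. These measures can reduce stable differences between areas, but not area-specific change over 18 months, and changing the random-effect level does not remove it either. The right response is a stated limitation.

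Third, the Discussion speaks of an opportunity to compare locations, not a powered test. A reader might conclude that location and ethnic group are inseparable. The article says only that each location has a specific concentration of migrants; it does not say that each holds one ethnic group, nor how many participants each has. That stronger claim is not supported.

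Fourth, the wording under Design and setting is loose syntax, since the abstract and the Control group section are clear. Agreed: that is editorial.

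**Conclusion.** The point holds as a mismatch between the unit of allocation and the named unit of clustering, with a conditional consequence. If wards are sub-units and the area ICC lies between 0.01 and 0.05, the false-positive rate is about 6% to 16% instead of 5%; with no area variance there is no inflation. If wards are the areas, the issue is only the reference distribution for three intervention clusters. Every ICC, the number of wards and the number of control areas are assumptions. Under either reading, the 80% in the sample size section is not the power of an analysis that respects the allocation unit.

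**What to change.** In Data analysis:

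- Define wards, and state how controls from each source are assigned to clusters.
- Make the allocation unit the top level of the multilevel model: residential area for the intervention group, and the corresponding municipality or area for controls. Keep wards as a lower level only if they are sub-units.
- Use small-sample degrees of freedom (Satterthwaite, or an area-level t reference).

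Elsewhere:

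- Under Limitations, state that area-specific changes over 18 months cannot be separated from the intervention effect, and that the model change does not cure this.
- In the Discussion, present the three-location comparison as descriptive.
- Reword Design and setting to agree with Control group.
- Do not present 80% as the power of this analysis.

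A further random effect for health worker is not needed for this correction; on top of three areas, and in one arm only, it may not be estimable.

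The cost is wider intervals and the lower power shown in the working. Baseline collection is reported complete, so areas cannot readily be added, and recruiting more people within the same three areas would not replace more areas. The changes themselves are to text and model only.

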### Recruitment of intervention participants

Intervention participants are identified, recruited, and selected by community health workers representing the elderly immigrant population. All community health workers have strong ties to and rootedness within the local migrant community. All elderly reached by the community health worker will be screened on the in- and exclusion criteria. Eligible elderly receive study information and an informed consent form in the preferred language for participation. If language problems make reading impossible, the community health worker reads the information to the potential participant. If the participant is not willing and/or not able to sign the written informed consent form, the community health worker holds the option of offering the potential participant the possibility for oral consentform. After permission, the community health worker makes an appointment for the baseline interview. In case of an informal care giver, the care giver is also invited by the community health worker to participate to measure care giver burden.

The community health workers do not conduct the interviews to avoid bias in the data collection. The interviews will be conducted by bilingual interviewers who are not involved in intervention activities. To ensure the examination of the intervention under real world circumstances no (financial) incentives will be offered for study participation.

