### Intervention programme

The intervention consists of four steps:

1. In the first step, the community health worker conducts home visits to the elderly to examine health problems, barriers to health care and social welfare services, and needs for adequate care. During the home visits, the community health worker registers the outcomes. The community health worker provides information on health and social welfare and refers to health and social welfare services if desirable. In addition to the home visits, information meetings are set up by the community health worker in collaboration with local migrant organisations.

2. In the second step, the community health worker identifies commonly shared problems based on the home visits and organises problem focused working groups of eight to twelve elderly persons (elderly who experience one of these problems), their family members/informal care givers, and local providers of health care and social welfare facilities.

3. In the third step, the community health worker co-operates with the elderly and providers of health care and social welfare services in finding solutions and in creating and conducting improvement programmes. These consist of concrete initiatives necessary for providing care and social welfare services that meet the health and social welfare needs of the elderly involved.

4. In the fourth step, these new initiatives will be implemented by the local providers of health care and social welfare facilities in their existing health care and welfare services in collaboration with the elderly. The community health worker monitors the process of implementation of the improvement programmes in the community.

Besides, the community health worker serves as participator in the research process by approaching participants for interviews.

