### Sample size calculation

No comparable interventions studies are available to determine the sample size. Therefore, we conducted a power analysis to determine the number of elderly based on a theoretical effect size assessed effect size. Based on research literature an effect size of 0.50 is estimated to provide a minimal clinically important difference [41]. We chose a moderate theoretical effect size of 0.40 to ensure that potential relevant findings are included. Power analysis showed that 97 elderly in each group should be included (an effect size of 0.40, an alpha of 0.05 and a beta of 0.20). Thus, we need a total of 194 elderly.

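### Community health workers group the intervention arm only, but the model corrects for wards only, so the planned 95% confidence intervals may be too narrow

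*Protocol article*

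**What the plan says.** The Data analysis section names one level of clustering: "To correct for the clustering of participants within wards and for baseline characteristics, multilevel analysis will be used". It adds: "Estimates will be performed with 95% confidence intervals". The term ward occurs nowhere else in the article. It is not defined, and it is not tied to the three residential areas, to the workers or to where the controls live. No worker level and no arm-specific variance is mentioned.

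Other sections show how the intervention arm is built. Under Recruitment of intervention participants: "Intervention participants are identified, recruited, and selected by community health workers representing the elderly immigrant population". Under Discussion: "we recruited several community health workers on each site to deliver the intervention". Under Intervention programme, the worker also visits people at home, informs and refers them, and "organises problem focused working groups of eight to twelve elderly persons" for those who share a problem.

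The Control group section says that controls have no worker and live outside the three areas. Turkish and Moroccan controls come from another ongoing study. Moluccan controls are recruited by bilingual interviewers together with a local welfare organisation.

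On size: "Power analysis showed that 97 elderly in each group should be included", based on "an effect size of 0.40, an alpha of 0.05 and a beta of 0.20".

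**The concern.** A worker reaches participants through his or her own network and then influences the primary outcome directly, by informing people about services and referring them. Participants who share a worker can therefore have correlated outcomes. There are several workers per site, so the worker is a level below site. That level exists in one arm only, which makes the data partially nested.

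A ward random intercept has, unless stated otherwise, one variance for both arms. It can stand in for worker variation only to the extent that workers and wards coincide. Where they do not, the variance of the intervention mean is understated. The standard error of the group contrast is then too small, and the false-positive rate rises above the nominal 5%.

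**Working it through.** **Inputs.** From the article: 97 per group, standardised effect 0.40, alpha 0.05 (two-sided assumed), beta 0.20, three intervention areas, several workers per site. Not in the article, so assumed: worker ICC 0.01 to 0.10, 6 to 12 workers in all, and the ward layout.

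**1. The plan's own figure.** n = 2 × (1.960 + 0.842)² / 0.40² = 98.1 per group, against 97 stated. Power at 97 is Φ(0.40 × √(97/2) − 1.960) = Φ(0.826) = 79.6%. The figure reproduces for independent participants. The standard error of the contrast is then √(2/97) = 0.144 SD.

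**2. Outer bound: no ward term at all.** With m participants per worker, in the intervention arm only:
- design effect DE = 1 + (m − 1) × ICC
- standard-error factor = √((1 + DE)/2)
- false-positive rate = 2 × [1 − Φ(1.96 / factor)]

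Twelve workers give m = 97/12 ≈ 8; six give m = 97/6 ≈ 16.

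| m | ICC | DE | SE factor | False-positive rate |
|---|---|---|---|---|
| 8 | 0.02 | 1.14 | 1.03 | 5.8% |
| 8 | 0.05 | 1.35 | 1.08 | 7.1% |
| 8 | 0.10 | 1.70 | 1.16 | 9.2% |
| 16 | 0.05 | 1.75 | 1.17 | 9.5% |
| 16 | 0.10 | 2.50 | 1.32 | 13.8% |

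The plan does have a ward term, so these rates are a bound and do not describe the planned analysis.

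**3. Ward-only model, workers cutting across wards.** This was simulated with REML, a continuous unadjusted outcome and normal-quantile intervals (4,000 runs).
- Six workers, ICC 0.05: mean reported standard error 0.151 to 0.156, true spread of the estimate 0.170 to 0.171, coverage 91.0% to 91.6%.
- Six workers, ICC 0.10: 0.150 to 0.156 against 0.189 to 0.193, coverage 87.4%.
- Nine workers: coverage 93.2% to 93.4% at ICC 0.05 and 89.8% to 90.7% at 0.10.
- ICC 0.01, six to ten workers: coverage 94.4% to 96.0%, so no visible harm.

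The true spread agrees with step 2 (0.144 × 1.17 = 0.168; 0.144 × 1.32 = 0.190). The reported standard error stays close to the independent value: a ward term does not pick up worker variance that is spread across wards.

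**4. Ward-only model, workers nested in wards.** In the same simulation, with worker ICC 0.05 to 0.10 and no other ward variance, coverage was 92.8% to 96.2%. Some intervals were too wide. A second run (2,000 runs, ward ICC 0.01, 15 control wards) gave less comfortable results. Six workers in three wards had false-positive rates of 7.2% (ICC 0.05) and 9.8% (0.10); one worker per ward, with six workers, gave 6.0% and 7.3%. Two causes are at work. The pooled ward variance is pulled down by many control wards without workers, and normal quantiles are too short with so few wards.

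**5. Small-sample degrees of freedom, and the added worker term.** With Satterthwaite degrees of freedom, ward ICC 0.01 and worker ICC 0.05 to 0.10 (600 runs; Monte Carlo standard error at 5% is √(0.05 × 0.95/600) = 0.9 points):

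| Model | False-positive rate |
|---|---|
| Ward only, workers cross wards | 6% to 13% |
| Ward only, workers nest in wards | 4.5% to 7% |
| Ward plus intervention-only worker term | 3.5% to 5.7% |

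The added term made intervals a few percent to about 27% wider.

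**The case against.** The strongest objection is that the ward term may already do the job. Nothing in the article says that workers cross ward lines, and its wording leans towards local nesting: workers are attached to a site, rooted in the local community and linked to a local welfare organisation. If ward means residential area, workers probably sit inside wards, and arm varies between wards. Step 4 shows that the shortfall is then small or absent. This stands, and it is why the point says may.

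A reader might infer four stronger things, none of which the article supports:
- That the intervals are definitely too narrow. This needs a ward layout that the article does not give.
- That the error rate is 5.8% to 13.8%. That range describes a model with no ward term.
- That the working groups add a further calculable excess. Membership is limited to people with a shared problem, so some participants may be in no group and others in several. Treating the whole arm as grouped in eights to twelves would overstate it.
- That every outcome is affected to this extent. Only a continuous, unadjusted outcome was checked. Adjustment for baseline would reduce correlation that comes from who was recruited, and self-reported care use may be a count or binary.

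It is also fair that controls are not free of recruiter grouping, given how the Moluccan controls are found. Only the delivery part of the worker effect is clearly confined to one arm, so a zero worker variance in controls is itself an assumption.

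Finally, one may say that random effects belong in a statistical analysis plan. That does not dispose of the point. The article commits to a clustering level and leaves out one that its own design creates.

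**Conclusion.** The point holds in conditional form. The design puts a worker level in the intervention arm only, and the stated model does not represent it. With an assumed worker ICC of 0.05 to 0.10 and 6 to 9 workers, the false-positive rate is about 6% to 13% if workers cut across wards. If they nest within wards it is close to nominal, about 4.5% to 7%. At an ICC near 0.01 the effect is negligible. The result rests on assumed values for the ICC, the number of workers and the ward layout, on a two-sided 5% test, and on a continuous unadjusted outcome. It should be settled before the analysis: the remedy is cheap, and the article leaves the reader unable to tell which case applies.

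**What to change.** In the Data analysis section:
- Keep the ward term and add a random intercept for community health worker that applies in the intervention arm only and is zero for controls.
- For continuous outcomes, use Satterthwaite degrees of freedom. For count or binary care use, use the equivalent generalised mixed model. Base the confidence intervals on these models.
- Link each intervention participant to the worker who recruited and visited them. The registration forms described under Process evaluation should supply this.
- Define ward, and state how wards relate to the three areas, to the workers and to the controls.

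Do not put working group in place of worker, because membership is partial and may overlap.

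The cost is analysis wording and one identifier column, with no new participants or measurements. Study status places the end of follow-up in December 2013, so the change can be made before analysis. The downside is somewhat wider intervals and a variance component estimated from few workers, which will itself be imprecise.
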